**Fig. 3 fig3:**
[figure not shown]
Example of the standard format for signal transduction pathway (STP) activity assay data presentation to the multidisciplinary tumour board. The figure shows curves of the STP activity of a cohort high-grade serous ovarian carcinoma (HGSC, n = 50) in red, a cohort of low-grade serous ovarian carcinoma (LGSC, n = 27) in purple and a cohort of Fallopian tube epithelium samples of healthy postmenopausal women (FTE_post, n = 9) in blue, for each of the seven measured STPs. The STP specific thresholds are defined as two standard deviations above the mean value of the STP activity measured in the Fallopian tube epithelium samples (n = 9). A. MAPK; mitogen activated protein kinase, B. ER; oestrogen receptor, C. AR; androgen receptor, D. HH; Hedgehog, E. TGFB; transforming growth factor beta, F. NOTCH, G. PI3K; phosphoinositide 3-kinase. (For interpretation of the references to colour in this figure legend, the reader is referred to the Web version of this article.)

### Multidisciplinary tumour board

2.7

The nationwide MTB will consist of gynaecological oncologists, medical oncologists and a translational researcher (trial manager). The MTB will decide on matched targeted therapy based on the STP activity assay results, their scientific experience and the available literature. STP activity results will be presented to the MTB in a standard format (Fig. 3). An MTB selection form has been developed to assist in guiding the selection of matched targeted therapy based on aberrantly activated STPs. In scenarios where multiple STPs show abnormal activation, a predefined set of questions within the selection form aids in decision-making. The form includes an assessment of which pathway exceeds the defined threshold value to the greatest extent, enabling prioritized inhibition of that particular pathway using targeted therapy. If the MTB decides the patient is eligible for matched targeted therapy, treatment will be initiated by the local clinician within 28 days. In case no aberrantly activated pathway is identified, the patient will receive standard of care.

### Interventions

2.8

Women diagnosed with tumours with aberrantly high activity of the ER, AR, PI3K or HH STP, will receive the following treatment with the recommended dosage (Fig. 2).•Treatment arm A (ER active tumours) with aromatase-inhibitor letrozole 2.5 mg daily.•Treatment arm B (AR active tumours) with anti-androgen bicalutamide 150 mg daily.•Treatment arm C (PI3K active tumours) with anti-fungal agent itraconazole 300 mg twice daily.•Treatment arm D (HH or concurrent HH and PI3K active tumours) with anti-fungal agent itraconazole 300 mg twice daily.

The selection of these targeted drugs was based on specific criteria. These criteria included demonstrated effectiveness in a subset of ovarian cancer patients or evidence of inhibition of pathway activity in cancer samples. Furthermore, all selected drugs were required to have received approval from the European Medicines Agency (EMA) for clinical use and be commercially available in the Netherlands. The drugs will be used outside their therapeutic indications during this study. A combination of two drugs targeting the ER and AR pathway is allowed if advised by the MTB (arm E) (Fig. 2).

Other STPs (TGF-β, Notch and MAPK) may be targeted during the study period by other available drugs, provided there is sufficient evidence for its use and safety. If deemed beneficial, the MTB could decide to open a new treatment arm (arm X) (Fig. 2).

### Pre-treatment evaluation before start of matched targeted therapy

2.9

Before the start of the recommended matched targeted therapy, patients will undergo a pre-treatment evaluation by their treating clinician. Baseline characteristics will be registered in the electronic case report form (eCRF). Furthermore, physical examination will be performed and the treating clinician will determine if any safety concerns exist. The treating clinician will assess if the patient has adequate renal and kidney function and checks for interactions between the matched targeted therapy and concomitant medication. Imaging of the tumour and evaluation by RECIST 1.1 of the tumour will be performed at baseline [31].

### Follow-up during matched targeted therapy

2.10

The treating clinician will be responsible for adequate follow-up during treatment with matched targeted therapy. Response will be evaluated at least every 12 weeks by imaging of the tumour according to RECIST 1.1 [31]. Additionally, physical examination and assessment of liver and kidney function are performed. Adverse events are evaluated according to the NCI CTCAE 5.0.

Both patients using matched targeted therapy, as well as patients who were not eligible to participate in the study and continued to receive standard of care, will be asked to complete the questionnaires to investigate health-related quality of life (QLQ-C30 and QLQ-OV28) [44], side effects (PRO-CTCAE) and cost-effectiveness (EQ-5D-5L) [45] at baseline, every 12 weeks during treatment and 12 weeks after the end of the treatment.

### End of treatment

2.11

In case of disease progression, patients will be withdrawn from the study and treatment with the matched targeted therapy will be ended. After disease progression, it is not possible to be included in the study for a second time; patients will receive standard (palliative) care. Patients will be asked to undergo a voluntary second biopsy to determine STP activity for research purposes after treatment has ended and before other systemic treatment has started.

## Results

3

### Outcome measures

3.1

The primary objective of this study is the progression-free survival (PFS) ratio (PFS2/PFS1 ratio) defined by the PFS on matched targeted therapy by STP activity assay (PFS2) in comparison to the PFS recorded on the therapy administered immediately prior to enrolment (PFS1) [31].

Secondary outcome measures include.•Proportion of patients with an actionable active STP for which targeted therapy is recommended in relation to the number of patients who underwent a biopsy.•Proportion of patients who receive matched targeted therapy in relation to the number of patients included in each study arm.•Best overall response defined by RECIST 1.1 based on radiological imaging [31].•One-year survival defined as the time from start matched targeted therapy till death or the end of the one-year follow-up period.•Overall survival defined as the time from start matched targeted therapy till death.•Predictive value of STP activity assay results (and if available, immunohistochemical biomarker analysis and DNA/RNA sequencing results) on matched targeted therapy response.•Change in STP activity score after disease progression (if available) compared to STP activity score before start of matched targeted therapy.•Side effects according to PRO-CTCAE™.•Health-related quality of life scored using standardized questionnaires from the EORTC (QLQ-C30 and QLQ-OV28) [44].•Cost-effectiveness will be calculated with health state utilities assessed in the standardized EuroQol 5D (EQ-5D-5L) questionnaire [45].

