### Study procedures

2.3

Informed consent will be obtained from the patients who are willing to participate and meeting the inclusion criteria. Subsequently, one histological biopsy will be collected to obtain tumour tissue for the STP activity assay. Patients are eligible for treatment with matched targeted therapy if an aberrantly activated STP is observed. Women with high activity of the ER, AR, PI3K or HH pathway will be included for treatment with either letrozole (arm A), bicalutamide (arm B), or itraconazole (arm C and D) (Fig. 2). These targeted drugs have been studied in ovarian cancer patients with acceptable side effects [[32], [33], [34], [35], [36], [37], [38], [39], [40], [41], [42]]. Patients who are not eligible to participate in the study will continue to receive standard of care by choice of the treating clinician. These patients are asked for consent to remain on study to complete questionnaires at baseline, every 12 weeks during the next course of treatment and 12 weeks after the end of treatment. Questionnaires are used for secondary analyses, such as side effects, quality of life and cost-effectiveness.

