### STP activity assay and determination of high STP activity

2.6

Using the annotated H&E slide as reference, tumour cells will be manually scraped off the study slides for the STP activity assay. Next, mRNA will be isolated from the tumour cells using the RNeasy FFPE Kit (Qiagen). Expression levels of pathway-specific target genes will be measured with real-time quantitative reverse transcription-PCR (RT-qPCR) analysis using the SuperScript III Platinum One-Step qRT-PCR Kit (Thermo Fisher Scientific) and commercially available OncoSIGNal 96-wells PCR plates (InnoSIGN). An internal quality control of reference genes is performed to confirm sufficient mRNA input for the assay.

STP activity assay provides a functional pathway activity score defined on a scale from 0 to 100, where the measured range of pathway activity may vary with the analysed tissue type. A score of 0 corresponds with the lowest odds of an active pathway and conversely 100 corresponds with the highest odds. In a prior study, we quantified the activity of STPs in epithelial cells derived from morphologically normal Fallopian tubes[29]. This analysis served as a basis to establish the reference levels for normal STP activity. We defined cut-off values for high STP activity in tumour samples, which were determined as two standard deviations above the mean value of STP activity measured in FTE samples. Individual STP activity assay results will be presented and analysed in a graph as shown in Fig. 3. This format contains the STP activity distributions measured in previous cohorts of normal FTE (blue curve), HGSC samples (red curve) and low-grade serous ovarian carcinoma (LGSC) samples (purple curve) [28,29,43]. For each measured STP, data is displayed in a single graph. The black dotted line represents the cut-off value for high STP activity. Before the start of the study, cut-off values will be updated to values in which the most recent results of the STP activity of the normal FTE are included. The individual STP activity measured in the patient's tumour sample will be plotted in the format. In case the individual STP activity transcends the cut-off (black dotted line), the STP will be classified as aberrantly activated. STP activity results will be sent to the principal investigators, who share the results with the multidisciplinary tumour board (MTB).

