### Plan of analysis

3.3

The proportion of patients who achieved a PFS2/PFS1 ratio ≥ 1.3 will be calculated from the total of patients that received matched targeted therapy. The primary endpoint will be tested by a one-sided exact test. Since histological subtype is a prognostic factor for PFS [36], subgroup analysis will be performed in case of adequate numbers.

Planned statistical analysis for the secondary outcome measures include the Kaplan-Meier survival curves tested with log-rank tests and Cox proportional hazard models for survival analysis. Furthermore, the predictive value of STP activity assay will be determined by correlations between STP activity scores and PFS2 using the Pearson or Spearman correlation coefficient. If patients undergo a voluntary second post-treatment biopsy, change in STP activity score will be calculated for each respective STP compared to the STP scores from the pre-treatment biopsy.

Using the appropriate algorithms, the side effects and health-related quality of life questionnaires will be analysed and compared accordingly between the group of patients that received matched targeted therapy and patients that received standard therapy. Together with the PFS, these results will be used in a quality adjusted life year calculation in order to calculate the cost-effectiveness and cost-utility ratios of matched targeted therapy. In addition, subgroup analysis per treatment arm will be conducted.

Descriptive statistics will be used to describe patient characteristics. Categorical variables will be expressed as a number with the percentage of the total study group. The chi-squared test or Fisher's exact test will be used to analyse associations between categorical variables. Continuous variables will be presented as mean with standard deviation or as median with interquartile range, whenever appropriate. A *t*-test or Mann-Whitney *U* test will be used to analyse associations between continuous variables.

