## Conclusion

4

This is the first study to evaluate the clinical implementation of *phenotype*-guided targeted therapy based on STP activity in tumour tissue of patients with recurrent ovarian cancer. Patients are treated with existing targeted drugs with tolerable toxicity profiles to investigate whether these drugs have therapeutic value beyond their approved indications. The unique study design allows for simultaneous screening for several promising treatment strategies and rapid incorporation of new cohorts based on other (off-label) targeted drugs or STPs. Intra-individual comparison of treatment response through the PFS ratio will limit confounders such as tumour histology. The results of this study will show the clinical applicability of STP activity to match recurrent ovarian cancer patients to targeted therapies.

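### Correlating the pathway score with PFS2 in treated, assay-high patients cannot show that the assay is predictive; the outcome and the conclusion should be narrowed

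*Protocol article*

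**What the plan says.** Treatment follows the assay. Study procedures states: "Patients are eligible for treatment with matched targeted therapy if an aberrantly activated STP is observed". The section on the STP activity assay sets the rule: "In case the individual STP activity transcends the cut-off (black dotted line), the STP will be classified as aberrantly activated", the cut-off being two standard deviations above the mean in normal Fallopian tube epithelium. For the remainder, Multidisciplinary tumour board states: "In case no aberrantly activated pathway is identified, the patient will receive standard of care".

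Interventions assigns letrozole to ER-active tumours (arm A) and bicalutamide to AR-active tumours (arm B). Itraconazole goes to PI3K-active tumours (arm C) and to tumours with HH active, alone or together with PI3K (arm D). ER and AR drugs may be combined (arm E).

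Outcome measures includes the "Predictive value of STP activity assay results (and if available, immunohistochemical biomarker analysis and DNA/RNA sequencing results) on matched targeted therapy response". Plan of analysis fixes the method: the predictive value "will be determined by correlations between STP activity scores and PFS2", by Pearson or Spearman coefficient. Outcome measures defines PFS2 as PFS on matched therapy.

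For patients not treated in the study, Study procedures says: "These patients are asked for consent to remain on study to complete questionnaires at baseline", and "Questionnaires are used for secondary analyses, such as side effects, quality of life and cost-effectiveness".

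The Conclusion states: "The results of this study will show the clinical applicability of STP activity to match recurrent ovarian cancer patients to targeted therapies". The abstract ends with a similar sentence about selecting patients.

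**The concern.** A marker is predictive if the benefit of the drug differs by marker level. That needs outcome on the drug at both low and high marker levels, and some way to take out the marker's link with prognosis under any treatment. Here the score decides who is treated, and the analysis uses treated patients only.

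Two misreadings follow. If high scores go with longer PFS2, slow-growing disease with a high score would produce the same pattern as drug sensitivity. If an arm beats the 15% null, the drug may be active whatever the score. Either result could be reported as support for selection by the assay. In the other direction, a weak correlation could be taken as a poor assay when only the upper part of the score range was examined.

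**Working it through.** **1. Who has PFS2, by score**

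| Drug | Score range among treated patients |
|---|---|
| Letrozole (A) | ER above cut-off only |
| Bicalutamide (B) | AR above cut-off only |
| Itraconazole (C) | PI3K above; HH not above, since concurrent activity goes to D |
| Itraconazole (D) | HH above; PI3K above or not |
| No active pathway | no study drug, so no PFS2 |

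No assay-high patient is allocated to a comparator. Nobody below the ER cut-off gets letrozole as ER-matched therapy, and the same holds for AR and bicalutamide. For these two drugs a high-versus-low contrast, a negative predictive value or a score-by-treatment interaction cannot be estimated at any sample size. What can be estimated is the proportion with a ratio of at least 1.3 among assay-high patients, and a score-outcome trend within them.

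**2. The plan's own sizes**

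Exact one-sided binomial test, null 0.15, alternative 0.30, alpha 0.10, n = 37, success at 9 or more: alpha 0.092, power 0.824. The smallest n with at least 80% power is 37, as stated. Biopsies: 148 / (0.5 × 0.9 × 0.9) = 365.4, i.e. 366, as stated. These sizes serve the primary endpoint; the article claims no power for the correlation.

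**3. Range restriction (illustration)**

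Assumptions not in the article: score and outcome bivariate normal; no censoring; correlation taken within an arm of 37; two-sided 5% test; full-range correlation ρ of 0.3 to 0.5. The share above one cut-off is not given. The article expects about 50% with any of four pathways active. That gives an average of 50% / 4 = 12.5% per pathway if none overlap, more if they do, and at most 50% for any one pathway.

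For a share s, let c be the normal quantile with upper tail s, and λ = φ(c)/s. The remaining score variance is u² = 1 + cλ − λ². The restricted correlation is r = ρu / √(1 − ρ² + ρ²u²). Power is approximately Φ(atanh(r) × √34 − 1.96).

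Example, s = 12.5%: c = 1.15, u = 0.427, u² = 0.18. For ρ = 0.4, r = 0.4 × 0.427 / √(0.84 + 0.16 × 0.182) = 0.18, and power is 0.19.

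| Share above cut-off | u | r for ρ = 0.3 / 0.4 / 0.5 | Power at n = 37 |
|---|---|---|---|
| No restriction | 1 | 0.30 / 0.40 / 0.50 | 0.44 / 0.70 / 0.89 |
| 50% | 0.603 | 0.19 / 0.25 / 0.33 | 0.19 / 0.33 / 0.51 |
| 25% | 0.492 | 0.15 / 0.21 / 0.27 | 0.14 / 0.24 / 0.37 |
| 12.5% | 0.427 | 0.13 / 0.18 / 0.24 | 0.12 / 0.19 / 0.30 |

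**4. What the design still offers**

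Arms C and D give the same drug to HH-low and HH-high patients: 37 against 37 if both fill, or 74 of the planned 148. The contrast is not randomised and is mixed with PI3K status, because all of arm C is PI3K-high and arm D need not be. The closest like-for-like comparison is arm C against the concurrent part of arm D, whose size the article does not give.

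Every treated patient also has PFS1. A score that tracks PFS1 as strongly as PFS2 looks prognostic. The planned correlation uses PFS2 alone and so drops the within-patient control on which the Sample size section relies.

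**The case against.** The strongest reply is that this is an ordinary biomarker-positive single-arm design. The outcome is one of ten secondary ones, is tied to response on matched therapy, and is defined openly as a correlation. Clinical applicability is a looser promise than predictive validity, and the feasibility outcomes bear on it too. This stands as far as it goes: the primary test does not depend on the correlation. It does not remove the point, because the article names the outcome predictive value, fixes an analysis that cannot deliver it, and states the conclusion without restriction.

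A reader might go further and infer that no assay-low patient receives a study drug. The itraconazole arms contradict this for HH, and PI3K status can vary within arm D. Nor is anyone selected on immunohistochemistry or sequencing, so the range-restriction argument does not apply directly to those markers; the prognostic one does.

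A reader might also infer that no analysis of treated patients can help. PFS1 gives a partial check. It is imperfect, because the biopsy is taken after the last standard treatment, so the score is measured after PFS1.

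Finally, one might hope that PFS in standard-care patients would settle the matter. It would not. Their scores lie mostly below the cut-offs and those of treated patients above, so a curved prognostic relation would look like an interaction. The article also describes only questionnaires for them.

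**Conclusion.** The point holds in a limited form. The planned correlation of score with PFS2 cannot separate predictive from prognostic association. For letrozole and bicalutamide the study cannot show that assay-low patients would benefit less. For itraconazole a non-randomised HH contrast exists and can be described.

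That much follows from the allocation rules and needs no numerical assumption. The loss of power does: under bivariate normality, with 12.5% to 50% above a cut-off and a full-range correlation of 0.4, power at 37 patients is 0.19 to 0.33 instead of 0.70. The lowest figure should not be quoted alone, because 12.5% is the average share only if pathways never overlap, and the article provides for multiple active pathways. If shares are unequal, a rarer pathway could lie below that value.

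The documents do not support saying that the study as a whole fails. Feasibility and the activity of each drug in assay-high patients can be assessed as planned. The change is advisable because it alters what may be concluded.

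**What to change.** - **Outcome measures:** restate the outcome as an exploratory association of STP score with outcome among assay-high patients treated with the matched drug.
- **Plan of analysis:** relate the score to the PFS2/PFS1 ratio. Show the score-PFS1 association beside score-PFS2 as a partial prognostic check, noting that the score was measured after PFS1. For itraconazole, describe outcome by HH status across arms C and D, with PI3K status shown, as a non-randomised comparison.
- **Abstract and Conclusion:** limit the claims to feasibility and to the activity of each drug in assay-high patients.
- **Standard-care patients:** draw no predictive claim from comparing them with treated patients; any such display should be descriptive only.

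The cost is a more modest claim and a little extra analysis of data that the primary endpoint already requires. Treatment, sample size and the primary endpoint do not change.

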**Study design:**

Patients with recurrent ovarian cancer and either 1) have platinum-resistant disease, 2) refrain from standard therapy or 3) are asymptomatic and not yet eligible for standard therapy will be included in this multi-centre prospective cohort study with multiple stepwise executed treatment arms. Targeted therapy will be available for patients with aberrantly high functional activity of the oestrogen receptor, androgen receptor, phosphoinositide 3-kinase or Hedgehog STP. The primary endpoint of this study is the progression-free survival (PFS) ratio (PFS2/PFS1 ratio) according to RECIST 1.1 determined by the PFS on matched targeted therapy (PFS2) compared to PFS on prior therapy (PFS1). Secondary endpoints include among others best overall response, overall survival, side effects, health-related quality of life and cost-effectiveness.

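### The 12-week questionnaire schedule gives patients who stop before week 12 no on-treatment side-effect form, and the CTCAE 5.0 data collected are tied to no listed outcome

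*Protocol article*

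**What the plan says.** Section 3.1 (Outcome measures) opens its list with "Secondary outcome measures include" and gives the side-effect item as "Side effects according to PRO-CTCAE™". The Abstract names side effects as a secondary endpoint without an instrument: "Secondary endpoints include among others best overall response, overall survival, side effects, health-related quality of life and cost-effectiveness".

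Section 2.10 describes two streams of tolerability data during matched therapy. The clinician's stream is "Adverse events are evaluated according to the NCI CTCAE 5.0", with "Additionally, physical examination and assessment of liver and kidney function are performed". The patient's stream is a set of questionnaires (QLQ-C30, QLQ-OV28, PRO-CTCAE, EQ-5D-5L) completed "at baseline, every 12 weeks during treatment and 12 weeks after the end of the treatment". Section 2.3 gives the same timing to patients who continue on standard care.

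Section 2.11 withdraws a patient from the study at disease progression and ends her matched therapy. Section 3.2 does not replace patients who withdraw after starting matched therapy and keeps them in the analysis.

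Section 3.3 says that "the side effects and health-related quality of life questionnaires will be analysed and compared accordingly" between matched-therapy and standard-therapy patients, and that these results, together with PFS, enter the quality-adjusted life-year calculation.

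**The concern.** The aim in the Introduction is longer survival with quality of life preserved, using drugs outside their indications that the Conclusion describes as tolerable. The tolerability evidence should therefore cover everyone who started treatment, including those who could not continue.

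The patient-reported outcome does not do that. The first on-treatment form falls at week 12, so the on-treatment data come only from patients still on the drug at that point. Those who stopped earlier, possibly because of side effects, remain in the analysis population with a baseline form and at best one form long after the last dose. The same gap affects quality of life and the utilities behind the cost-effectiveness result. An on-treatment reading that was not taken cannot be recovered later.

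The stream that would fill part of the gap is the clinician's grading and the liver and kidney tests. It is collected, but the article links it to no outcome and no analysis. A patient questionnaire cannot register an abnormal laboratory value.

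**Working it through.** **1. What a patient who stops early contributes.** Take a stop for toxicity at week 5. The forms due are baseline and 12 weeks after the end of treatment, that is week 5 + 12 = week 17. The week-12 on-treatment form is never due. If she stops for progression at week 8, the later form would fall at week 8 + 12 = week 20, but section 2.11 has by then withdrawn her from the study. Sections 2.10 and 2.11 do not say whether that form is still completed.

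**2. How many patients this could be.** The article gives no time on treatment, so this is an assumption shown over a range. The planned number is 4 arms × 37 = 148 (section 3.2), which agrees with the stated total. With an exponential time on treatment and median *m* months, and 12 weeks = 84/30.44 = 2.76 months:

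share stopping before week 12 = 1 − 0.5^(2.76/*m*)

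| Assumed median (months) | Share stopping before week 12 | Of 148 |
|---|---|---|
| 2 | 0.616 | 91 |
| 3 | 0.471 | 70 |
| 4 | 0.380 | 56 |
| 6 | 0.273 | 40 |

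These are upper-end figures. The exponential model lets stops fall at any time, whereas section 2.10 says "Response will be evaluated at least every 12 weeks by imaging of the tumour according to RECIST 1.1". Many progression stops would then be called at about week 12, when the questionnaire is also due. The range also counts stops for every reason, not only toxicity.

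**3. Whether the missing forms bias the result within an arm.** Let *f* be the share stopping early, *a* the toxicity rate among them and *b* the rate among patients who reach week 12. The on-treatment forms show *b*. The rate in all who started is *f·a* + (1 − *f*)·*b*. Illustration with assumed values *f* = 0.25 and *b* = 0.20:

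- *a* = 0.40: 0.25 × 0.40 + 0.75 × 0.20 = 0.25, against 0.20 seen.
- *a* = 0.60: 0.25 × 0.60 + 0.75 × 0.20 = 0.30, against 0.20 seen.
- *a* = 0.20: 0.25 × 0.20 + 0.75 × 0.20 = 0.20, so no bias.

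The result is too favourable only if early stoppers have more toxicity than the others. That is plausible, but the article gives no figure for it.

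**4. The comparison with standard care.** Sections 2.3 and 2.10 put both groups on the same 12-week schedule, so each loses its own early stoppers. The net direction depends on which group loses more patients with toxicity. The article does not say, and the bias could run either way.

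**5. Collected data against declared outcome.** Section 2.10 collects CTCAE 5.0 grades and organ function. The side-effect item in section 3.1 names PRO-CTCAE, the side-effect analysis in section 3.3 is of questionnaires, and section 2.3 likewise names questionnaires as the source for side effects. No listed outcome or stated analysis uses the clinician-graded or laboratory data.

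**The case against.** The strongest reply is that toxicity is captured anyway. Clinicians grade adverse events by CTCAE 5.0 and check liver and kidney function throughout matched therapy. The outcome list is worded as open. A journal article may leave adverse-event tables to the full protocol or the analysis plan, and nothing in this one says the CTCAE data will go unreported. It is also coherent to use the questionnaire for the comparison with standard care, since it is the only side-effect instrument the article describes for both groups. A 12-week schedule aligned with imaging is a legitimate choice.

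Most of this stands, and it limits the point in three ways. A reader might infer that the trial cannot show liver or kidney toxicity; section 2.10 shows that it can, and only the link to an outcome and an analysis is absent from the article. A reader might infer that tolerability will certainly look too good; that depends on early stopping being related to toxicity, and the bias is nil if it is not. A reader might infer that the comparison with standard care is tilted towards matched therapy; with the same schedule in both groups, no direction is established.

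The reply does not remove the schedule gap. The timing is stated explicitly in sections 2.3 and 2.10, so it is a choice the article makes and not a detail it leaves out. CTCAE grades cannot stand in for missing quality-of-life or EQ-5D-5L readings.

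**Conclusion.** The point holds in a limited form. The patient-reported schedule leaves anyone who stops before week 12 without an on-treatment side-effect, quality-of-life or EQ-5D-5L reading, and the form due after treatment is uncertain once a patient has progressed. The number affected cannot be found from the article: 27% to 62% (40 to 91 of 148) rests on an exponential time on treatment with a median of 6 down to 2 months, and is upper-end because of the imaging schedule. Within an arm, on-treatment tolerability may look too favourable if early stopping is related to toxicity; the size of any such bias is not estimable from the article.

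The missing link between the CTCAE 5.0 data and a listed outcome is the lesser part, since the full protocol may supply it. Neither part affects the primary endpoint or the interim rules. The change is worth making because it is cheap and the lost readings are irrecoverable.

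**What to change.** 1. In section 2.10, and in the matching text of section 2.3, add one questionnaire set at the time treatment stops for any reason, in both the matched-therapy and the standard-care groups. State in section 2.11 whether the form 12 weeks after the end of treatment is still completed after withdrawal for progression. Cost: one extra set per patient, a small burden, and an amendment to the questionnaire schedule.

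2. In sections 3.1 and 3.3, report the CTCAE 5.0 events already collected, including liver and kidney laboratory grades, per arm in all patients who started matched therapy, alongside PRO-CTCAE. Keep PRO-CTCAE for the comparison with standard care. Cost: wording and tables only, since section 2.10 already provides for the data.
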